## INTRODUCTION

### Background

ST-segment elevation myocardial infarction (STEMI) is a life threatening, time-sensitive condition consisting of a sudden complete blockage of a coronary artery. It requires treatment within 30-90 minutes, and the diagnosis is made via electrocardiogram (ECG). Patients suspected of STEMI are referred to an emergency department (ED) for rapid evaluation, diagnosis, and treatment. Guidelines recommend the diagnosis be made within 10 minutes of arrival. However, the first 10 minutes of an ED visit typically consist of registration and triage. The median door-to-doctor time for an ED patient is 60 minutes. As a result, ED registration and triage staff use screening criteria to identify patients who should receive an early ECG to identify STEMI. To date, the test characteristics of the screening process have not been extensively investigated. This study will examine whether there is variation in STEMI screening performance in different EDs, and whether variability is associated with the comprehensiveness of the screening criteria used.

Chest pain is the classic symptom for STEMI, however 20-30% of STEMI patients do not report chest pain. Appropriately comprehensive STEMI screening criteria, used to trigger an early ECG (trigger criteria), should include more information than chest pain presence or absence. Ideal STEMI case capture occurs when trigger criteria also includes atypical symptoms like shortness of breath and dizziness; associated symptoms like jaw pain, neck pain or back pain; and considerations of the patient's age. Previously collected data suggest the inclusion of these characteristics in different EDs trigger criteria varies significantly. We hypothesize there is variability in the screening processes between institutions, and this variability is associated with different diagnostic test characteristics.

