### **Potential Risks and Benefits**

The ED is the unit of observation in this study. As a result, the data consists of aggregate numbers representing ED patient care events in 2014. Protected health information (PHI) and patient level data may be reviewed within the local ED to get the aggregate numbers we will use to calculate screening performance. Related data extraction will use the administrative reporting functions within the hospitals' electronic medical record systems (EMR) and review of existing summative data reports from the hospitals' STEMI case review committees. As a result there is limited potential for study-related breaches in PHI confidentiality, thus presenting minimal risk to the EDs and their patients. The participating EDs are involved in this study as a quality improvement effort with the intent to publish the results as research. The benefit to the EDs, and the patients they serve, is gaining knowledge about their local practice in the context of national peers to inform their current clinical STEMI screening practices. There is no compensation for participation.

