### **SAMPLE SIZE**

Seven EDs will be included. In 2014 these EDs saw 64353, 59929, 53165, 155000, 68621, 46378, 60000 patients. This results in a total of 507446 patients screened for STEMI. Based on previously reported data, and Vanderbilt's 2014 data, the incidence of STEMI is approximately 0.14-0.18%. Using the median estimate of 0.16% we anticipate 812 STEMI cases.

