### **FINAL ANALYSIS PLAN**

Two-by-two contingency tables will be calculated for each ED, and all EDs combined (Table S2). The data will be reported as sensitivity, specificity, negative predictive value, positive predictive value, false negative rate, false positive rate, likelihood ratio of being screened for an early ECG (positive index test) if the ECG demonstrates STEMI (positive reference test), likelihood ratio of being screened for an early ECG (positive index test) if the ECG does not show STEMI (negative reference test). This data will then be correlated with the inclusion of atypical symptoms, associated symptoms or age (representing yes or no as binary values) in the trigger criteria via a multi-variate logistic regression to see if there is an association.

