## SURVEY

1) ED Name: [drop down menu]

- Select one
- Brigham and Women's Hospital
- Hospital of the University of Pennsylvania
- Vanderbilt University
- University of Wisconsin
- University of Texas Southwestern
- Oregon Health & Sciences University
- University of California - Davis

2) Please upload a copy of your IRB approval letter as a pdf file.

3) In 2014, how did you identify arriving ED patients for an early ECG to screen for STEMI?

[drop down menu]

- Select one
- Established registration/triage criteria or protocol
- Solely at the discretion of the registration staff or triaging provider

*\*EDOSG Baseline Data Collection Tool Question #41*

4) If you have an established early ECG protocol that serve as your “trigger criteria,” upload a PDF or MS Word document including the criteria/policy for which patients get an early ECG to screen for STEMI.

5) In addition to “chest pain” what elements are included in your early ECG screening trigger criteria to identify patients for an early ECG? Select all that apply:

- Atypical STEMI symptoms (shortness of breath, dyspnea on exertion, fatigue, nausea)
- Associated STEMI symptoms (arm pain, jaw pain, back pain, epigastric pain, abdominal pain)
- An age threshold
- Other
- Not applicable. We do not have an established trigger criteria

6) What was the total number of patients,  $\geq 18$  years of age, seen in the ED in 2014? Include all individuals registered as ED patients. Do not exclude the following ED dispositions: eloped, left without being seen, left before completing treatment, left AMA.

<<Free text response>>

7) In 2014, what was the total number of patients ( $\geq 18$  years of age) that had an ECG performed  $\leq 15$  minutes after their arrival in the ED?

<<Free text response>>

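### Survey question 5 omits dizziness and neck pain, which the Background gives as examples of the exposures, and no check of the site ticks is stated, so an ED could be miscoded among only seven

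*Protocol*

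**What the plan says.** The protocol describes the symptom exposures in two places. The Background says that good case capture needs criteria with "atypical symptoms like shortness of breath and dizziness; associated symptoms like jaw pain, neck pain or back pain", together with the patient's age. Survey question 5 then asks each site to tick what its criteria contain besides chest pain. One box is "Atypical STEMI symptoms (shortness of breath, dyspnea on exertion, fatigue, nausea" and another is "Associated STEMI symptoms (arm pain, jaw pain, back pain, epigastric pain, abdominal pain", each list standing in brackets. There are further boxes for an age threshold, for 'Other', and for having no established criteria.

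The Final Analysis Plan relates screening performance to "inclusion of atypical symptoms, associated symptoms or age (representing yes or no as binary values) in the trigger criteria" by regression. It has no term for 'Other' and does not name the survey item that supplies the yes/no values, but question 5 is the only item that records them in that form. Question 4 asks sites with an established protocol to upload it. Nothing in the protocol says that the uploads will be used to code or check question 5.

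Potential Risks and Benefits states that "The ED is the unit of observation in this study", and Sample Size that "Seven EDs will be included".

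**The concern.** The yes/no values are the only exposures for the second of two objectives. If the instrument that collects them leaves out symptoms that the protocol itself uses to illustrate the categories, a site may read the bracketed list as complete. It would then put dizziness or neck pain under 'Other', and the ED would enter the analysis as unexposed although the Background would count it as exposed.

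The outcome side has more protection. Under Data Collection, STEMI counts are compared between the medical record and the STEMI committee, and discrepancies go to chart review, with the declared aim of limiting misclassification. That review covers trigger and STEMI status of cases, not the content of the criteria. The exposure ticks sit in the same survey, under the same site investigator, as the counts in questions 6 to 9. They are therefore neither verified nor made blind to performance.

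With a handful of EDs, one wrong yes/no value can shift the estimated association noticeably.

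**Working it through.** **The lists side by side**

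| Category | In both places | Background only | Question 5 only |
|---|---|---|---|
| Atypical | shortness of breath | dizziness | fatigue, nausea, exertional dyspnea |
| Associated | jaw pain, back pain | neck pain | arm, epigastric and abdominal pain |

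The Background names five symptoms, and question 5 carries three of them. Because the value is yes/no per category, the omission changes an ED's coding only if dizziness is its sole atypical item, or neck pain its sole associated item, and the site does not tick the box on its label alone.

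**The plan's own figures.** Sample Size gives the volumes: "In 2014 these EDs saw 64353, 59929, 53165, 155000, 68621, 46378, 60000 patients". They sum to 507,446, and 507,446 x 0.0016 = 811.9, which agrees with "Using the median estimate of 0.16% we anticipate 812 STEMI cases". The protocol gives no exposure split, effect size or power for the second objective, so everything below is conditional on assumptions.

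**Weight of one ED.** Counted equally: 1/7 = 14%. By volume: from 46,378/507,446 = 9.1% to 155,000/507,446 = 30.5%.

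**One miscoded ED, unadjusted contrast.** The share of the true contrast that is retained is

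P(truly yes | coded yes) - P(truly yes | coded no).

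Assume that 4 EDs are truly 'yes' with sensitivity S + 10 points, that 3 are truly 'no' with sensitivity S, and that EDs have equal weight.

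- One 'yes' coded 'no' (the error that the omission would cause): the coded-no mean is S + 10/4 = S + 2.5. The observed difference is 10 - 2.5 = 7.5 points, so 25% is lost.
- One 'no' coded 'yes': the coded-yes mean is S + 40/5 = S + 8. The observed difference is 8.0 points, so 20% is lost.

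**Other splits, one value flipped in either direction**

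| Split | Retained, equal weights | Retained, volume weights |
|---|---|---|
| 3/4 or 4/3 | 75-80% | 51-88% |
| 2/5 or 5/2 | 67-83% | 39-90% |
| 1/6 or 6/1 | 50%; in 1 of 7 flips no variation is left | 23-77% |

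The 23% extreme arises, for example, when the smallest ED is the only exposed one and the largest is wrongly coded as exposed: 46,378/(46,378 + 155,000) = 0.23.

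**Three exposures together.** A simulation drew 20,000 random full-rank designs of seven EDs with three binary exposures, fitted a linear model, and flipped one exposure in one ED.

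- In about 5% of designs the coefficient could no longer be estimated.
- In the rest, the median retained share was 75% (5th to 95th percentile 45% to 108%).
- In about 6% of the estimable designs the coefficient was inflated; in none did it change sign.
- Part of the effect moved to the other two exposures.

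**The case against.** The strongest reply is that there is nothing here to contradict. The Background introduces its symptoms with 'like', so they are examples in introductory prose. The Key Definitions define neither category, and a longer list in the survey is not an error. This stands: a reader might infer that question 5 departs from a formal protocol definition, and the documents do not support that. What remains is narrower. The only item that records the exposures drops two of the five symptoms used to illustrate them, and does not say that its bracketed lists are open.

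The second reply is that miscoding would be rare. This also stands. Shortness of breath, jaw pain and back pain appear in both places, most criteria that go beyond chest pain are likely to include one of the shared items, and nothing shows that any of the seven EDs depends on dizziness or neck pain alone.

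The third is that the source and coding of the exposure belong in the statistical analysis plan, that question 4 already gathers the policies, and that a biostatistician reviewed the questionnaire. This stands in part. A later plan could add central coding, and the uploads make it possible. It cannot change the wording that sites have answered.

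The fourth is that the illustration is not the planned analysis. That is correct: it is an unadjusted difference in sensitivity, whereas the objective concerns likelihood ratios in a multivariable regression. It shows how sensitive seven units are to one error and does not forecast the bias.

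That site investigators might tick boxes to suit known performance is speculation. The document offers no evidence for it, only the absence of separation.

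**Conclusion.** The mismatch is real and minor. Question 5 omits dizziness and neck pain, 'Other' has no place in the analysis, and the uploaded policies have no stated role in checking the ticks. An ED that relies only on an omitted item within a category could therefore be recorded as 'no'.

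If that happened to one ED of seven, 20-25% of an unadjusted contrast would be lost under an assumed 4/3 split with equal weights (25% for the 'yes' coded 'no' direction). The loss could be smaller or larger under volume weighting or a less balanced split. In a three-exposure model the distortion is usually toward zero, but not always.

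A reader might go further and conclude that the second objective will be materially diluted. The documents do not support this. They give no exposure split or effect size, show no miscoded ED, and present overlapping lists that make such an ED uncommon. This is an inexpensive improvement to the instrument and its handling, not a flaw that undermines the study.

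**What to change.** Two changes.

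1. Add dizziness to the atypical list and neck pain to the associated list in question 5, so that every symptom named in the Background appears there. This concerns how exposures are recorded, not which symptoms an ED should act on.
2. Have existing coordinating-centre staff set the symptom exposure values from the question 4 documents before they open the 2x2 counts, and use the question 5 ticks as a cross-check. If sites have already answered the survey, this step alone deals with most of the problem.

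The cost is a wording change and the reading of at most seven policies that are already being collected. Two limits remain. EDs without a written policy still rely on question 5. The Vanderbilt counts are already printed in Table S1, so coding that ED without knowledge of its performance is only partly achievable.

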### **Study Objectives**

This study has two objectives. It will first examine whether the STEMI screening performance observed at Vanderbilt is generalizable. We will do this by calculating 2x2 contingency table data for patients seen in six additional EDs (in different regions of the country) individually, and then as a total population combined with Vanderbilt. Second, it will determine whether STEMI screening performance improves with more data incorporated into the trigger criteria by identifying whether there is an association between positive and negative likelihood ratios with the inclusion of associated symptoms, atypical symptoms, and age in the trigger criteria.

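### The single yes/no age item can pool age rules that widen the early-ECG trigger with rules that narrow it, so the age association may cancel or be misread as an effect of comprehensiveness

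*Protocol*

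**What the plan says.** The second objective (Protocol, Study Objectives) asks whether "STEMI screening performance improves with more data incorporated into the trigger criteria", judged by the "association between positive and negative likelihood ratios with the inclusion of associated symptoms, atypical symptoms, and age in the trigger criteria". The Background section lists age with the symptom groups as part of good case capture: "and considerations of the patient's age". The Study Outcome section then describes the construct as the comprehensiveness of the criteria.

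The predictors come from survey question 5, which asks, beyond chest pain, "what elements are included in your early ECG screening trigger criteria to identify patients for an early ECG". One of its tick-boxes is "An age threshold". It asks for neither a cut-off nor what the threshold does. The Final Analysis Plan relates performance to the "inclusion of atypical symptoms, associated symptoms or age (representing yes or no as binary values) in the trigger criteria", using a multivariable logistic regression.

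Survey question 4 asks each ED with an established protocol to upload its criteria. Nothing in the protocol says that these documents will be abstracted or used to code the predictors.

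**The concern.** The three yes/no predictors are treated as the same kind of thing: an extra element that makes the criteria more complete. For the two symptom groups this is coherent, because adding an alternative trigger can only add patients to the early-ECG group. An age threshold has no fixed direction. A rule under which age brings in patients without chest pain widens the trigger. A rule under which a symptom counts only above an age narrows it. Both tick the same box and both become age = yes.

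Two consequences are possible. If both kinds occur among the seven EDs, their effects can offset each other, and the age term may show nothing although every rule has an effect. If all age = yes sites narrow, nothing is mixed, but LR+ can rise because the trigger is tighter. That rise could be reported as a benefit of more comprehensive criteria while sensitivity has fallen.

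Only the second objective is affected. The 2x2 estimates for each ED and for all EDs combined do not use the age code.

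**Working it through.** **Inputs.** Table S1: TP 60, FP 13,092, FN 15, TN 55,454. The sizes of the age-rule effects are assumptions, since the protocol gives none.

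**Reproducing the plan's figures.** Sensitivity = 60/75 = 80.0%. Specificity = 55,454/68,546 = 80.9% (the table rounds to 81%). Both agree. From these, LR+ = 0.800/0.191 = 4.19 and LR- = 0.200/0.809 = 0.247. The Rationale section states 5.2 and 0.025, which do not follow from Table S1. That is a separate matter, and the Table S1 counts are used here.

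**Narrowing rule** (assumed to drop 5% of true positives and 30% of false positives):
- TP = 57, FN = 18, FP = 13,092 x 0.70 = 9,164, TN = 59,382.
- Sensitivity = 57/75 = 76.0%; specificity = 59,382/68,546 = 86.6%.
- LR+ = 0.760/0.1337 = 5.68; LR- = 0.240/0.8663 = 0.277.

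**Widening rule** (assumed to pick up one third of false negatives and 10% of true negatives):
- TP = 65, FN = 10, FP = 13,092 + 5,545 = 18,637, TN = 49,909.
- Sensitivity = 65/75 = 86.7%; specificity = 49,909/68,546 = 72.8%.
- LR+ = 0.8667/0.2719 = 3.19; LR- = 0.1333/0.7281 = 0.183.

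**Range of assumptions.** Narrowing drops 2-10% of TP and 20-40% of FP. Widening picks up 20-50% of FN and 5-20% of TN.

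| | Sensitivity | Specificity | LR+ | LR- |
|---|---|---|---|---|
| Table S1 | 80.0% | 80.9% | 4.19 | 0.247 |
| Narrowing | 72-78% | 85-89% | 4.7-6.8 | 0.24-0.33 |
| Widening | 84-90% | 65-77% | 2.4-3.9 | 0.13-0.25 |

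Sensitivity, specificity and LR+ move in opposite directions throughout this range. LR- usually does, but not always. At one corner of narrowing (2% of TP, 40% of FP) it falls slightly, to 0.244. At one corner of widening (20% of FN, 20% of TN) it stays at 0.247.

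**When the directions hold.** The odds ratio in Table S1 is (60 x 55,454)/(15 x 13,092) = 16.9.
- Narrowing raises LR+ when the share of FP dropped exceeds the share of TP dropped. It raises LR- when (share of TP dropped)/(share of FP dropped) is above 1/16.9 = 0.059.
- Widening lowers LR+ when (share of FN gained)/(share of TN gained) is below 16.9. It lowers LR- when that ratio is above 1.

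**Pooling under one code.** Treat the age contrast as the mean log ratio to Table S1 among age = yes sites, with sites otherwise alike. For LR+, ln(5.684/4.189) = +0.305 for narrowing and ln(3.187/4.189) = -0.273 for widening.
- One of each: (0.305 - 0.273)/2 = +0.016, a factor of 1.02.
- Two narrowing, one widening: (0.305 + 0.305 - 0.273)/3 = +0.112, a factor of 1.12.
- One narrowing, two widening: (0.305 - 0.273 - 0.273)/3 = -0.080, a factor of 0.92.

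For LR-, one of each gives (0.115 - 0.300)/2 = -0.093, so cancellation there is only partial. Among three age = yes sites, the type of a single site sets the sign for LR+.

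**The case against.** The strongest reply is that the protocol speaks of more data and more information, not of a wider trigger. On that reading an age rule is added information whichever way it acts, and a yes/no code matches the question asked. This has force. A reader might infer that only rules which add patients should count as comprehensive, but the documents do not say so, and narrowing is the type that raised LR+ above, one of the two measures in the objective. The reply does not rescue the pooled term, which still joins rules with opposite expected effects on that same measure.

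Four further readings go beyond the documents:
- **That the age effect does mix directions.** No section shows that any of the seven EDs uses a restricting threshold, and the wording of question 5, beyond chest pain, leans toward added elements without excluding a restriction.
- **That an age-gated symptom rule is coded the same as an ungated one.** Age is a separate term, so a gated site ticking both boxes differs from an ungated site with no age rule. Only the symptom term is shared.
- **That LR- always moves in opposite directions.** The range above shows exceptions.
- **That the age result would be uninterpretable.** With seven EDs and three binary predictors it is imprecise under any coding, and the Study Outcome section already promises only a description.

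It can also be said that question 4 collects the needed policies and that abstraction rules belong in a statistical analysis plan. The first part is right, and it makes repair easy. The second is weaker here, because the protocol itself fixes the predictor as yes/no and describes no use of the uploads.

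**Conclusion.** The point stands as a risk built into a stated coding rule. One age box with yes/no coding can combine rules that move sensitivity, specificity and LR+ in opposite directions, and usually LR- too. Under the mid-range assumptions LR+ goes from 4.19 to 5.68 or to 3.19, and one site of each kind averages to a factor of 1.02. If every age site narrows, LR+ still rises to 5.68 while missed STEMI cases go from 15 to 18 of 75, which could be credited to comprehensiveness.

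This rests on assumed effect sizes applied to one site's table, and on sites being otherwise alike. Whether both kinds of rule, or any narrowing rule, occur among the seven EDs cannot be told from the documents. The consequence is limited to one of three predictors in one of two objectives, but the correction is cheap enough to be worth making.

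**What to change.** Have the coordinating center abstract, from each policy uploaded under survey question 4, the direction and cut-off of any age rule. If the survey has not yet been sent, also split the age box in question 5 into two, one for age adding patients and one for age limiting patients, each with its cut-off.

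In the Final Analysis Plan, do not pool the two types under one yes/no age term. Report them separately and descriptively, and show sensitivity and specificity beside LR+ and LR- so that a tighter trigger can be recognised as such. This concerns coding and reporting only, and takes no position on which age rule an ED should use.

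The cost is a reading of at most seven documents already requested, and possibly one reworded survey item. The drawback is fewer EDs in each age category, so the age result is descriptive only.

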## PERFORMANCE OF STEMI SCREENING TRIGGER CRITERIA

Online form available at: <https://redcap.vanderbilt.edu/surveys/?s=ET3WK99HDM>

---

The electrocardiogram (ECG) is often described as a screening test for ST-elevation myocardial infarction (STEMI), with coronary angiography as the criterion standard diagnostic test. However, in the emergency department (ED), treatment is initiated based on the presence of STEMI on ECG. In addition, timely diagnosis should be made within 10 minutes, well before a patient is seen by a physician and during the processes of registration and triage. As a result, in the context of ED patient care processes and flow, the ECG is the **diagnostic test** and the clinical criteria used to screen arriving ED patients for STEMI in during registration and triage (ECG trigger criteria) is the true **screening test**.

This study seeks to quantify the screening performance of the early ECG trigger criteria used to screen for STEMI across 7 geographically diverse EDs. The screening population includes all ED patients  $\geq 18$  years of age seen in the ED from January 1, 2014 at 12:00am to December 31, 2014 at 11:59am. It assumes that all ECGs done within the first 15 minutes of an ED visit are to screen for STEMI. The **STEMI screening criteria** is the index test. Triggering an early ECG is a positive index test. An **early ECG** (performed  $\leq 15$  minutes after patient arrival) is the reference diagnostic test standard. An ECG demonstrating STEMI is a positive reference test. Patients, who do not receive an early ECG from registration or triage, go on to receive typical ED care. This provides an opportunity to identify cases missed by the index test, making typical ED care an alternative reference standard for trigger negative patients.

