### Key Definitions

Trigger positive = early ECG to screen for STEMI = an ECG performed  $\leq 15$  minutes of arrival

Arrival = first documented presence or time-stamp of the patients presence in the ED

EMS = patients coming to the ED via emergency medical system (EMS) ambulance or helicopter

Walk-in = patients coming to the ED via non-EMS transportation

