8) What was the total number of 2014 STEMI cases that came through the ED? Include all patients,  $\geq 18$  years of age, who were registered as ED patients? This is either all ED patients with an ED admission or hospital discharge diagnosis of STEMI (via an electronic medical record query for diagnosis “STEMI” or ICD9 codes 410.01, 410.11, 410.21, 410.31, 410.41, 410.51, 410.61, 410.81, 410.91). Confirm this number with your hospital STEMI Case Review Committee. If there is a discrepancy, review the individual patient charts. Based on Vanderbilt data, the incidence of STEMI reported in the literature, and all participant ED patient volumes, there should be no more than 5 cases that require review.

<<Free text response>>

9) What was the total number of 2014 STEMI cases that came through the ED that did not get an early ECG (ECG  $\leq 15$  minutes of arrival)? These are the missed screening cases. This can be obtained as an adjudicated case count from your hospital STEMI committee. Many STEMI quality improvement committees will document time-to-ECG permitting an assessment of those missed by screening. These should not include patients whose were screened, but had STEMI-negative early ECGs.

<<Free text response>>

10) What was the total number of 2014 ED patients who had both an ECG performed and a serum troponin ordered and resulted. This is an estimate of the underlying “chest pain patient” burden.

<<Free text response>>

|                                                                                                                                                                                                                                                                      | Greeter               | Check-in Kiosk        | Registration Clerk    | Triage RN             | Midlevel Provider     | Physician             | Other                 |
|----------------------------------------------------------------------------------------------------------------------------------------------------------------------------------------------------------------------------------------------------------------------|-----------------------|-----------------------|-----------------------|-----------------------|-----------------------|-----------------------|-----------------------|

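### Table S2 counts patients who left before evaluation as true negatives, and the survey does not count them, so no bound can be put on the missed-case rate

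*Protocol*

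**What the plan says.** **Denominator.** Protocol, SURVEY, question 6 asks for the adults seen in 2014 and adds "Include all individuals registered as ED patients". It then says "Do not exclude the following ED dispositions: eloped, left without being seen, left before completing treatment, left AMA".

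**Index test.** Key Definitions: "Trigger positive = early ECG to screen for STEMI = an ECG performed" within 15 minutes of arrival. Everyone else is trigger negative.

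**Reference standard.** The section PERFORMANCE OF STEMI SCREENING TRIGGER CRITERIA uses two standards. For those with an early ECG, "An ECG demonstrating STEMI is a positive reference test". For the rest, "Patients, who do not receive an early ECG from registration or triage, go on to receive typical ED care", which is said to allow missed cases to surface, "making typical ED care an alternative reference standard for trigger negative patients". The Rationale makes the same argument. Neither place makes an exception for patients who leave.

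**Cases.** Question 8 counts STEMI by diagnosis: "This is either all ED patients with an ED admission or hospital discharge diagnosis of STEMI". The number is checked with the hospital STEMI committee. Question 9 takes the part of those cases that had no early ECG: "These are the missed screening cases".

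**Table S2.** The cells are TP = #8-#9, FP = #7-#8+#9, FN = #9 and TN = #6-#7-#9.

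None of survey questions 1 to 25 asks how many patients left before evaluation.

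**The concern.** The trigger-negative row rests on the premise that patients passed over by the screen are later evaluated, so that a missed STEMI would come to light. For a trigger-negative patient who left without being seen, that premise fails: there was no early ECG and no typical ED care. Disease status is unknown, yet the subtraction in Table S2 puts the patient among the true negatives.

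The consequence runs in one direction. If any of these patients had a STEMI that was never recognised, it is missing from #8 and #9. Sensitivity is then too high, and the missed-case rate and LR- are too low. The missed-case rate is a named result under Study Outcome, and LR- is one of the two measures that the second objective relates to the content of the criteria. Without a count of these patients, the study cannot say how much its results depend on them.

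**Working it through.** **Inputs.** From Table S1 (Vanderbilt, 2014): TP 60, FP 13,092, FN 15, TN 55,454, total 68,621. From Sample Size: planning incidence 0.16%. The share of visits that are trigger negative and left unevaluated is not in the documents; 2% to 5% is an assumption.

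**1. Reproduce the plan's figures.** Sensitivity = 60/75 = 80.0%. Specificity = 55,454/68,546 = 80.90%. Accuracy = (60 + 55,454)/68,621 = 80.90%. These match the 80%, 81% and 81% in Table S1. With #6 = 68,621, #7 = 13,152, #8 = 75 and #9 = 15, the Table S2 formulas return 60, 13,092, 15 and 55,454 exactly. LR- = (1 - 0.800)/0.8090 = 0.247. (The Rationale prints 0.025 for LR-; that is a separate discrepancy, and the Table S1 value is used here.)

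**2. Effect of one hidden case.** Moving k unrecognised STEMIs from TN to FN gives sensitivity = 60/(75 + k). For k = 1 this is 60/76 = 78.9%; for k = 2, 60/77 = 77.9%; for k = 5, 60/80 = 75.0%. Each hidden case costs about 1 point, because only 75 cases carry the estimate.

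**3. Expected number of hidden cases.** k = u × r, where u is the number of unverified trigger-negatives and r their STEMI rate. The lower r is the observed trigger-negative rate, 15/55,469 = 0.027%. The upper r is 0.16%.

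| Unverified share | u | r | k | Sensitivity | Missed-case rate | LR- |
|---|---|---|---|---|---|---|
| None (as planned) | 0 | n/a | 0 | 80.0% | 20.0% | 0.247 |
| 2% | 1,372 | 0.027% | 0.37 | 79.6% | 20.4% | 0.252 |
| 5% | 3,431 | 0.027% | 0.93 | 79.0% | 21.0% | 0.259 |
| 2% | 1,372 | 0.16% | 2.20 | 77.7% | 22.3% | 0.275 |
| 5% | 3,431 | 0.16% | 5.49 | 74.5% | 25.5% | 0.315 |

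**4. Specificity.** In the most extreme row, (55,454 - 5.49)/(68,546 - 5.49) = 80.899%, against 80.900% as planned. The change is under 0.002 points.

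**5. Would excluding the leavers help?** Removing 5% from TN gives specificity (55,454 - 3,431)/(68,546 - 3,431) = 52,023/65,115 = 79.9%. Sensitivity stays at 60/75 = 80.0% and the missed-case rate at 20.0%. Exclusion therefore leaves the affected measures unchanged, and it lowers specificity almost wholly by discarding genuine negatives.

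**The case against.** The strongest reply is that question 6 is right as written. Screening takes place at registration and triage, and Subject Inclusion covers everyone screened. Leaving is a later event, and removing people because of it would select on something that happened after the index test. This stands: keeping all registered arrivals is a defensible screened population. A reader might infer that leavers should come out of the true-negative cell; step 5 shows that this would not touch sensitivity or the missed-case rate.

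Other stronger readings are also unsupported:

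- **Specificity is materially inflated.** At the rates used here, more than 99.8% of leavers are real negatives, and step 4 shows a negligible effect.
- **A leaver's STEMI can never be counted.** Question 8 does not require the diagnosis to be made at the visit the patient left, and under Data Collection the STEMI committee also reports missed cases. A patient who returned to the same hospital might be captured, although no link back to the earlier visit is described.
- **The problem is beyond repair once the survey closes.** The study is retrospective, and sites could query dispositions again. It is simply cheaper to ask once.
- **All four dispositions in question 6 are unverified.** Patients who left AMA or before completing treatment may have been evaluated. The point is firm only for those who left before evaluation.
- **Walk-outs distort the second objective.** This would require walk-out rates to differ between EDs, and the documents give no figures.

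It is also fair to say that 74.5% lies inside the 95% Wilson interval for 60/75 (about 70% to 87%). But that interval describes chance variation at one site. The shift here has one direction, and it would not shrink as the pooled analysis approaches the 812 cases expected under Sample Size.

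Finally, a bounds analysis is commonly left to a SAP, which is not at hand. A SAP could specify one, but the survey as written would not supply the count it needs.

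**Conclusion.** The point holds as a modest one. Unevaluated trigger-negative leavers are counted as disease-free, contrary to the protocol's own reason for accepting typical ED care as a reference standard, and no survey item shows how many there are. Any bias is towards higher sensitivity and a lower missed-case rate and LR-.

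At the Table S1 site, under the assumed 2% to 5% share, sensitivity would fall from 80.0% to between 79.6% and 79.0% at the trigger-negative rate. At 0.16% it would fall to between 77.7% and 74.5%. That second range is an upper bound on the effect, because it applies a whole-population rate, about six times the trigger-negative rate (0.16/0.027), to people the screen had already passed over. If no leaver had a STEMI, there is no bias in sensitivity, missed-case rate or LR-. The documents cannot settle which case applies, and they do not support changing the study population or the main table.

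**What to change.** Keep all registered arrivals and the Table S2 cells as the main analysis.

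1. Add one survey item after question 7: the number of adults with no ECG during the visit who left before clinician evaluation (left without being seen, or eloped before evaluation). Do not include patients who left after being evaluated.
2. For each ED and pooled, report a bound on sensitivity, missed-case rate and LR-. Multiply this count by a stated range of STEMI rates, from the trigger-negative rate up to 0.16%, and move the product from true negative to false negative. Because the cases only move between two cells of the same row, the total and the trigger margins are unchanged.
3. State as a limitation that typical ED care was not applied to these patients.

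The cost is one extra aggregate EMR count per site and a slightly less favourable lower bound beside the main estimates.
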